All patients over 18 years of age scheduled to undergo a CE of the small bowel for any indication at London Health Sciences Centre will be considered for recruitment.

Inclusion Criteria

1. Any patient undergoing small bowel CE for any indication

Exclusion Criteria

1. Patients with a contraindication to CE (GI tract stricture, oropharyngeal dysphagia, pregnancy)
2. Endoscopic insertion of the capsule
3. Inpatient procedures for active GI bleeding
4. Patients with fluid restrictions or those who believe they would be unable to drink up to 900 ml of fluid within 10 minutes prior to the VCE

Intervention

All patients will take a standard small bowel preparation consisting of the following starting the day before the procedure: clear fluids starting at lunch, two liters of PEG at 8 PM, and fasting starting at midnight. Patients arrive in the endoscopy unit at 6:45 AM the following morning. Randomization is performed via REDCap and simethicone given as follows: those randomized to high volume simethicone will drink a 750 ml solution (1125 mg simethicone diluted in 750 ml of water, 1.5 mg/ml) and those randomized to standard volume simethicone will drink a 200 ml solution (300 mg simethicone diluted in 200 ml of water, 1.5 mg/ml) in identical non-transparent lidded cups sealed with tamper tape prepared by the hospital’s Clinical Trials Pharmacy and administered to the patient by the research nurse. Regardless of randomization results, the solution will be consumed over a 5 minute period and the patient instructed to resume fasting for 30 minutes before swallowing the capsule. Adherence will be assessed by collection of the cups after ingestion.

After swallowing the capsule, the patient is discharged from the endoscopy unit, encouraged to remain active for the day, allowed to have clear fluids in 2 hours, a light meal in 4 hours, and to return the CE recorder to the endoscopy unit at 5 PM. Once the CE recorder is returned, the patient is discharged from the endoscopy unit and has completed the study. Subjects will be called by the study nurse 7 days later to assess for adverse events.

CE will be performed with the Given Imaging SB3 capsule and reviewed with the accompanying software, RAPID v8.3. Videos will be reviewed in a blinded fashion without knowledge of randomization results using the Park score ([41](#_ENREF_41)) as follows:

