1. First duodenal and first cecal image are marked. The interval between these two landmarks defines the small bowel transit time.
2. The small bowel transit time is manually divided into 5 minute intervals and the first image of every 5 minute interval is selected. For example, if the first duodenal image occurred at 13 minute 52 second, the next image is selected at 18 minute 52 seconds followed by 23 minute 52 seconds and so forth until the cecum is reached.
3. Each selected image is given a visualized mucosa score and degree of obstruction score as follows:
   1. Visualized Mucosa Score (VMS)
      1. 3 points: >75% of mucosa is seen
      2. 2 points: 50-75% of mucosa is seen
      3. 1 point: 25-49% of mucosa is seen
      4. 0 point: <25% of mucosa is seen
   2. Degree of Obstruction Score (DOS)
      1. 3 points: <5% of view is obstructed
      2. 2 points: 5-25% of view is obstructed
      3. 1 point: 26-50% of view is obstructed
      4. 0 point: >50% of view is obstructed
4. The visualization quality score (VQS) is calculated as follows:
   1. VQS = (mean VMS + mean DOS) / 2
5. The VMS, DOS, and VQS will be assessed based on the following segments:
   1. Total small intestine (0-100% SI transit time)
   2. Proximal half of the small intestine (0-49% SI transit time)
   3. Distal half of the small intestine (50-100% SI transit time)

Baseline Data Collection

The following information will be collected at the time of enrollment: hospital ID number, age, sex, indication, previous relevant investigations (i.e upper endoscopy, colonoscopy, small bowel imaging), and risk factors for intestinal dysmotility (history of diabetes, scleroderma, or medications including anticholinergics and opioids).

Outcome Measures

*Primary outcome*

1. Adequate bowel preparation defined as VQS > 2.25 ([41](#_ENREF_41))

*Secondary outcomes*

1. Mean Park score
2. Diagnostic yield
   1. Any of the following lesions will be considered diagnostic: angioectasia, polyp, tumor/mass, ulcer, Crohn’s disease, stricture
   2. Note that small non-specific red spots of questionable significance will not be considered diagnostic
3. Study completion rate
   1. Defined as the capsule reaching the cecum
4. Gastric emptying time
   1. Defined as the time interval between the first gastric and first duodenal image
5. Small intestinal transit time
   1. Defined as the time interval between the first duodenal and first cecal image

Adverse Events

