Since simethicone is a non-absorbable over-the-counter medication, we do not anticipate any adverse events. In addition, there are no contraindications or adverse events noted in the Compendium of Pharmaceuticals and Specialties nor were there any seen in our pilot study. However, any possible adverse events will be assessed at the time of the procedure and through a phone call 7 days later. Minor adverse events will be defined as: any new (or worsening if chronic) abdominal pain, bloating, flatulence, constipation, diarrhea, nausea. Serious adverse events will be defined as any symptom resulting in an emergency room visit, hospitalization, or death.

Regulatory Approval

We have already secured regulatory approval and a No Objection Letter from Health Canada (control #190759) and our local Research Ethics Board (HSREB #106269). We recently submitted amendments based on a revised sample size and the amendments are currently under review. However, we do not anticipate any regulatory barriers should this grant application be funded.

Statistical Analysis

Baseline demographic data following a normal distribution will be reported as mean and standard deviation (SD) while non-parametric data will be reported as median and range. Categorical data will be presented as proportions. Differences in continuous outcomes will be analyzed with t-test (if normally distributed) and Wilcoxon rank sum test (for non-parametric data). Differences in categorical outcomes will be analyzed with Chi-square test or Fisher’s exact test as deemed appropriate. All data will be analyzed as intention to treat.

The sample size was calculated using conservative estimates from our pilot study as follows: assuming 80% adequacy rate in the experimental arm (87% in pilot study), 60% in the control arm (53% in pilot study), a two sided significance level of 0.05, and power of 0.80, 164 participants are needed in the study.

Study Strengths & Limitations

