| **Degree of Obstruction Score (DOS)**  <5%  5-25%  26-50%  >50% | **Score**  3  2  1  0 |
| **Visualization Quality Score** | (Mean VMS + Mean DOS)/2 |

**Table 2:** Park Score ([41](#_ENREF_41))

|  | **Standard Volume Simethicone**  **(n = 15 )** | **High Volume**  **Simethicone**  **(n = 15)** |
| --- | --- | --- |
| Age-mean (SD) | 60.8 (15.7) | 65.5 (19.4) |
| Female-no. (%) | 6 (40%) | 7 (47%) |
| Indication-no. (%)  Obscure overt gastrointestinal bleeding  Obscure occult gastrointestinal bleeding  Crohn’s disease  Small bowel mass | 6 (40%)  7 (47%)  1 (7%)  1 (7%) | 5 (33%)  7 (47%)  -  3 (20%) |
| Risk factors for intestinal dysmotility-no. (%)  Narcotics  Anti-cholinergic  Calcium channel blocker  Diabetes  Primary autonomic dysfunction | 4 (27%)  2  1  3  -  - | 9 (60%)  -  -  3  5  1 |
| Prior tests of the small intestine-no. (%)  Capsule endoscopy  SBFT  CT abdomen  MR enterography  Small bowel ultrasound  Meckel’s scan | 4 (27%)  2 (13%)  -  4 (27%)  -  1 (7%)  1 (7%) | 4 (27%)  1 (7%)  -  4 (27%)  2 (13%)  -  - |

**Table 3:** Pilot study baseline demographics

|  | **Standard Volume Simethicone**  **(n = 15)** | **High Volume**  **Simethicone**  **(n = 15)** | **p-value** |
| --- | --- | --- | --- |
| Gastric transit time-mean (SD) | 21.9 (30.8) | 40.9 (31.8) | 0.11 |
| Small intestine transit time-mean (SD) | 251.0 (81.5) | 214.9 (119.3) | 0.34 |
| Incomplete study-no (%)^a^ | 0 (0%) | 1 (7%) | 0.31 |
| Visualized Mucosa Score-mean (SD)  Proximal half  Distal half  Entire small intestine | 2.53 (0.37)  2.28 (0.53)  2.45 (0.37) | 2.69 (0.33)  2.48 (0.24)  2.64 (0.18) | 0.21  0.19  0.08 |
| Degree of Obstruction Score-mean (SD)  Proximal half  Distal half  Entire small intestine | 2.17 (0.40)  1.90 (0.59)  2.09 (0.39) | 2.29 (0.48)  2.07 (0.36)  2.24 (0.32) | 0.47  0.34  0.25 |
| Visualization Quality Score-mean (SD)  Proximal half  Distal half  Entire small intestine | 2.35 (0.37)  2.09 (0.56)  2.23 (0.45) | 2.49 (0.40)  2.28 (0.27)  2.44 (0.24) | 0.32  0.25  0.13 |
| Adequate bowel preparation^b^ | 8 (53%) | 13 (87%) | 0.05 |

^a^Denotes failure to reach the cecum prior to the end of the study

^b^Defined as visualization quality score for the entire small intestine ≥ 2.25

**Table 4:** Pilot study results

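### Small intestinal transit time has no value when the capsule misses the cecum, and the plan gives no rule for these patients; dropping them would bias the comparison towards shorter times in the arm with more incomplete studies

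*Combined protocol and SAP*

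**What the plan says.** Under Outcome Measures, small intestinal transit time is a secondary outcome: "Defined as the time interval between the first duodenal and first cecal image". Study completion is a separate secondary outcome: "Defined as the capsule reaching the cecum". The plan therefore expects some capsules not to get there.

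Under Intervention, observation is finite. Patients are asked to "return the CE recorder to the endoscopy unit at 5 PM".

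Under Statistical Analysis, the whole rule for continuous outcomes is "Differences in continuous outcomes will be analyzed with t-test (if normally distributed) and Wilcoxon rank sum test (for non-parametric data"), followed by a general statement that analysis is by intention to treat. No section says what time, rank or censoring status a patient receives when the cecum is not seen.

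The pilot results (Table 4) had one such patient, in the high-volume arm. The table's footnote describes an incomplete study thus: "Denotes failure to reach the cecum prior to the end of the study".

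**The concern.** A capsule still in the small bowel when recording stops has a transit time known only to exceed what was recorded. The definition gives it no number, and both named tests need one. An analyst who follows the text literally leaves it out. The capsules left out are the slow ones, so the arm with more incomplete studies looks faster than it is.

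High volume could then appear to speed transit, or a true slowing could be hidden, only because of which patients contributed a value. With no rule written down, the choice can also be made after the data are seen.

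**Working it through.** **1. The plan's own figures.** The sample size concerns the primary outcome only (60% vs 80%, two-sided 0.05, power 0.80). With pooled variance, n per arm = [1.96·√(2·0.7·0.3) + 0.8416·√(0.6·0.4 + 0.8·0.2)]² / 0.2² = (1.270 + 0.532)² / 0.04 ≈ 81.2. This rounds up to 82 per arm, or 164, as stated. No power is given for transit.

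**2. How the pilot handled its incomplete study.** Table 4 gives 251.0 (81.5) for standard volume and 214.9 (119.3) for high volume, p=0.34. No unit is given; minutes are assumed. T-tests from these summaries give:

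| n | pooled | Welch |
|---|---|---|
| 15 vs 15 | 0.341 | 0.343 |
| 15 vs 14 | 0.347 | 0.355 |

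The reported value fits 15 vs 15. If a t-test was used, the incomplete capsule was apparently entered as a finished time, or n=15 was used by default. The table does not say which.

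The two readings have different consequences:
- If 214.9 is the mean of 14 completers, adding the last capsule at an assumed 400 to 570 min gives (14·214.9 + 400)/15 = 227.2 to (14·214.9 + 570)/15 = 238.6. The gap of 251.0 − 214.9 = 36.1 min then shrinks to between 23.8 and 12.4 min.
- If the capsule was already counted at its last image, with a 570-min window and the arm's mean gastric time, its entry was about 570 − 40.9 = 529.1 min. Raising it to 570 moves the mean by only (570 − 529.1)/15 = 2.7 min.

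**3. Recording window.** Arrival is at 6:45 AM. Adding 5 min to drink and 30 min of fasting, swallowing is at 7:20 AM at the earliest, so 5 PM is at most 580 min later. The documents give no recording length. Windows of 570 and 480 min are assumed.

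**4. Bias in the mean difference (high minus standard).** Simulated lognormal small-bowel times; gastric times from the pilot (21.9 (30.8) and 40.9 (31.8)); small-bowel window = recording window minus gastric time.

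| Scenario | Window | Incomplete, standard vs high | True | Dropped | Truncated |
|---|---|---|---|---|---|
| Equal means 251, SDs 81.5 and 119.3 | 570 | 0.6% vs 3.3% | 0 | -11 | -3 |
| same | 480 | 2.4% vs 7.6% | 0 | -17 | -7 |
| High volume 20% slower: 251 vs 301, SDs 119.3 and 143 | 570 | 2.8% vs 7.3% | about 50 | 33 | 43 |
| same | 480 | 6.4% vs 14.8% | about 50 | 26 | 38 |

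The equal-means rows concern means only. With unequal SDs the lognormal medians already differ: 251/√(1 + (81.5/251)²) ≈ 239 against 251/√(1 + (119.3/251)²) ≈ 227.

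**5. Wilcoxon power, 82 per arm, high volume 20% slower.**

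| Handling | 570 min | 480 min |
|---|---|---|
| No censoring | 0.70 | 0.71 |
| Incompletes ranked longest | 0.70 | 0.70 |
| Truncated times | 0.70 | 0.65 |
| Incompletes dropped | 0.57 | 0.44 |

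The log-rank test gives 0.64 at both windows.

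**6. Expected numbers.** The pooled pilot rate is 1/30, and 164/30 ≈ 5 patients. The estimate is very imprecise: the exact 95% interval for 1/15 alone runs from 0.2% to 32%.

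**7. Gastric emptying.** It is undefined only if the capsule never leaves the stomach during recording. In the simulation this happened in at most about 0.03% of patients.

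**The case against.** The strongest reply is that the plan names a test that copes. A rank test can place incomplete capsules last, and even truncated times lose little, because a capsule still in the small bowel late in the day already ranks near the top. The intention-to-treat sentence also points away from dropping patients. Completion rate is reported alongside, and transit time appears in none of the three Specific Aims.

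Most of this stands. The named tests do not force the error, and the real harm comes from dropping. But the plan does not say that incompletes are ranked, the intention-to-treat sentence supplies no value for them, and the definition read literally excludes them.

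A reader might also infer more than the documents support:
- **That high volume causes more incomplete studies.** This would rest on one event, 1/15 vs 0/15, p=0.31.
- **That the pilot's 36-min gap is an artefact.** The reported p-value fits 15 vs 15, so the incomplete capsule may already have been counted. The larger shifts in step 2 are a worst case.
- **That gastric emptying has the same problem.** The footnote concerns the cecum, and nothing shows that any capsule stayed in the stomach.
- **That a log-rank test must replace the planned tests.** It has less power here than the rank approach. Applied to small-bowel transit it is also censored informatively, since a long gastric time shortens the remaining window.

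**Conclusion.** The gap is real but limited to small intestinal transit time. An incomplete study has no value under the definition, and the plan supplies none. If such studies are dropped, a true mean difference of 0 becomes about -11 to -17 min, and a true difference of about 50 min shrinks to 26 to 33 min. If truncated times are compared as means, 0 becomes about -3 to -7 min. A Wilcoxon test on truncated times is little affected.

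These sizes rest on lognormal times, pilot means and SDs from 15 patients per arm, and windows of 480 to 570 min. The direction in the equal-means case follows from the larger pilot SD and longer gastric time taken for the high-volume arm, neither of which is established. What does not depend on those figures is the mechanism: dropping slow capsules shortens transit in whichever arm has more of them.

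The primary outcome test and N=164 are untouched.

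**What to change.** In Statistical Analysis, state that small intestinal transit time is compared in all randomised patients by the Wilcoxon rank sum test, with capsules not reaching the cecum ranked longest. Report medians and the number incomplete per arm.

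Add, as a sensitivity analysis, a Kaplan-Meier analysis of time from swallowing to cecum, censored at the last recorded image. Starting the clock at swallowing avoids the informative censoring caused by long gastric times, and it keeps patients with no duodenal image in the analysis.

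Fix the wording before allocation is revealed. The cost is slightly more analysis work, and means are replaced by medians. No extra data collection or patients are needed, because the image times are already in the recording.

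### The planned comparisons are valid but leave collected baseline data unused; a prespecified adjusted analysis could add up to about 7 points of power, depending on unknown prognostic strength

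*Combined protocol and SAP*

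**What the plan says.** The Statistical Analysis section covers all categorical outcomes, including the primary adequacy outcome and diagnostic yield, in one sentence: "Differences in categorical outcomes will be analyzed with Chi-square test", with Fisher's exact test as the alternative. For continuous outcomes it says: "Differences in continuous outcomes will be analyzed with t-test (if normally distributed) and Wilcoxon rank sum test (for non-parametric data"). No model or covariate is named there or elsewhere. Randomization & Blinding describes blocks of varying size and names no stratification factor.

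Baseline Data Collection lists age, sex, indication and previous investigations, together with "risk factors for intestinal dysmotility (history of diabetes, scleroderma, or medications including anticholinergics and opioids"). These items are given no role in the analysis.

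Specific Aim #2 compares the Park score by segment, and its hypothesis is about the mean score in each segment.

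Table 3 (pilot demographics) reports a row headed "Risk factors for intestinal dysmotility-no": 4/15 in the standard-volume arm and 9/15 in the high-volume arm. Its sub-rows include calcium channel blockers (3 and 3) and primary autonomic dysfunction (0 and 1). Baseline Data Collection names neither.

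**The concern.** The trial has about 80% power and draws on 100 funded capsules a year, so precision is hard to buy with more patients. If a recorded baseline variable predicts adequacy, adjusting for it narrows the interval without recruiting anyone. Adjustment has to be settled in advance. If an imbalance is noticed after unblinding, an unplanned adjusted analysis will look chosen for its result.

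The Park-score analysis raises a separate point. Choosing between a t-test and a Wilcoxon test on normality means the data decide which quantity is compared. A rank test does not estimate the difference in means that Aim 2 asks about.

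**Working it through.** **1. The plan's own figure.** Inputs, from Statistical Analysis: "assuming 80% adequacy rate in the experimental arm (87% in pilot study"), "60% in the control arm (53% in pilot study"), and "a two sided significance level of 0.05, and power of 0.80, 164 participants are needed in the study". Allocation of 1:1 is assumed, because the ratio is not stated.

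n per arm = [1.96·√(2·0.7·0.3) + 0.8416·√(0.6·0.4 + 0.8·0.2)]² / 0.2² = 3.249/0.04 = 81.2, rounded up to 82. The total is 164, which reproduces. Power at 82 per arm is 80.4%.

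**2. What adjustment could add (approximate formula).** If the covariates explain a share R² of the outcome variance, the variance of the risk difference is multiplied by (1 − R²). The effective size is then 82/(1 − R²) per arm. R² is not in the documents, so a range is assumed:

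| R² | Power at N = 164 |
| --- | --- |
| 0 | 80.4% |
| 0.05 | 82.4% |
| 0.10 | 84.4% |
| 0.20 | 88.4% |

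For one yes/no covariate with prevalence 13/30 (pilot, both arms) and a gap d in adequacy, R² = (13/30)(17/30)d² / [0.5·(0.24 + 0.16)] = 0.2456·d²/0.20. A gap of 10 points gives R² = 0.012 (power 80.9%), 20 points gives 0.049 (82.3%), and 30 points gives 0.11 (84.8%).

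**3. Simulation.** Settings: 82 per arm, adequacy 60% against 80%, one covariate with prevalence 0.43, adjusted risk difference with robust standard error, 3,000 trials per setting. The Monte Carlo error of each power is about √(0.8·0.2/3000) = 0.7 points.

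| Assumed odds ratio | Unadjusted | Adjusted |
| --- | --- | --- |
| 1 | 81.5% | 81.4% |
| 0.5 | 80.8% | 82.0% |
| 0.35 | 80.3% | 81.6% |
| 0.25 | 80.3% | 84.2% |
| 0.15 | 81.0% | 87.1% |

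With no treatment effect, the adjusted test rejected in 4.1% to 5.6% of trials. Adding an age term unrelated to outcome cost nothing when neither covariate was prognostic (80% to 81%), and the gains were about 1 to 7 points over odds ratios of 0.5 to 0.15. Seven useless covariates did cost a little: 81.4% fell to 79.6%.

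**4. Is the model too large?** Expected inadequate preparations are 82·0.4 + 82·0.2 = 49, for three coefficients besides the intercept. That is comfortable.

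**5. Chance imbalance.** The SD of the difference in prevalence is √(2·(13/30)(17/30)/82) = 7.7 points, so 95% of imbalances lie within 1.96·7.7 = 15 points. At odds ratios of 0.35 and 0.25 the adequacy gap is 25 and 32 points in the control arm but 17 and 22 in the high-volume arm, an average of 21 and 27. The largest likely shift is therefore 0.15·21 to 0.15·27, or about 3 to 4 points. The unadjusted interval has half-width 1.96·√(0.24/82 + 0.16/82) = 1.96·7.0 = 14 points, and it already includes this variation.

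**6. The dysmotility definition.** Table 3 has 15 risk-factor entries (2 + 1 + 3 in the standard-volume arm, 3 + 5 + 1 in the high-volume arm), and 6 of them are calcium channel blockers. Counting only items named in Baseline Data Collection leaves 5/15 against 2 or 3 of 15. Prevalence then falls from 43% to between 7/30 = 23% and 8/30 = 27%.

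**The case against.** The strongest reply is that nothing is broken. The chi-square test is valid under randomisation, it matches the sample-size basis, and 164 reproduces. All of that stands. It is also true that the documents never relate dysmotility or indication to adequacy, Park score or yield, and do not say why these items are recorded. A gain in precision therefore cannot be promised.

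A reader might infer from the pilot's 60% against 27% that dysmotility matters or that the main trial will be unbalanced. The documents support neither. The split is compatible with chance (Fisher p = 0.14), and a 33-point gap at 82 per arm has a probability of about 0.00002. The arm with more risk factors also had the better preparation. Only 2 of its 15 patients were inadequate, so at least 7 of its 9 risk-factor patients were adequate.

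A reader might also take the unequal pilot SDs of the Park score (0.45 and 0.24) to invalidate the t-test. With equal arms they do not: simulated type I error at 82 per arm was 4.96%. The case for a linear model rests on the target of Aim 2.

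Finally, it can fairly be said that the baseline list is introduced with a non-exclusive word, so calcium channel blockers may still be captured under medications. That is why the definition needs fixing; it does not show that the item is missing.

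**Conclusion.** This is an improvement at almost no cost, and it corrects no error. The planned primary test keeps its validity and its 80% power. A small prespecified adjustment would add about 0 power points if the covariates are not prognostic, 1 to 4 at odds ratios of 0.5 to 0.25, and about 7 at 0.15. These figures assume 1:1 allocation, 82 per arm, adequacy of 60% and 80%, and 43% prevalence from the pilot's wider definition. The odds ratios are assumptions. Because the prognostic strength is unknown, the result does not justify a smaller sample. Chance imbalance, at about 3 to 4 points under the assumptions above, should not be read as bias on top of the unadjusted interval.

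The Park-score point stands without any assumption about covariates: the aim concerns means, and the planned switch can replace that comparison with one that does not estimate them.

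**What to change.** Before unblinding, add the following to Statistical Analysis:

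- **Primary outcome.** Fit a logistic model with arm, any dysmotility risk factor (yes/no) and age. Report the standardised (marginal) risk difference with 95% CI and p-value. The odds ratio alone would change the target to a conditional effect. Keep the unadjusted chi-square test as a sensitivity analysis and N at 164.
- **Covariates.** Keep them few. If indication is added for diagnostic yield, group it into a few categories, since the pilot had cells of 0, 1 and 3.
- **Park scores.** For each segment, use a linear model with the same covariates and robust standard errors. Report the mean difference and 95% CI, and drop the normality-based choice of test.
- **Definition.** State one list of dysmotility risk factors, say whether calcium channel blockers and primary autonomic dysfunction count, and record whatever the list includes.

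The cost is a few sentences of analysis text, slightly more analysis work and possibly one extra baseline tick-box. No patients or procedures are added.
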